### Secondary endpoint analyses

Descriptive statistics will be used to summarize the presence and concentration of **autoantibodies** in the cohorts. Regression models will explore potential associations between autoantibody levels and pain severity, adjusting for confounding variables such as age, gender, and disease type. Model assumptions for these regression analyses will be examined using the same diagnostic framework as for the primary endpoint, and, where appropriate, autoantibody concentrations will be transformed to better meet normality assumptions. This analysis may reveal immune-mediated mechanisms that contribute to persistent pain in certain individuals.

Clustering techniques will be applied to **phenotype data** to identify subgroups of participants who share similar clinical characteristics. These subgroups will then be analysed for differences in pain severity, pain location (using body maps), and wearable sensor data. Correlations between phenotypic clusters and genetic data will be assessed to explore potential genetic underpinnings of each phenotype.

Descriptive statistics will be provided for **body map-based** pain location frequencies [22,44], stratified by variables such as age group, diagnosis, gender, and pain interference scores. Hierarchical clustering will be used to discover novel pain phenotypes [45]. We will pre-specify the distance metric (Euclidean distance on scaled variables) and linkage method, and we will report the criteria used for selecting the final number of clusters, so that the clustering procedure can be replicated. Incomplete body map data will not be included in descriptive statistics, but the degree of missingness will be quantified and analysed for associations with other parameters, such as age and pain location.

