The **primary endpoint** will focus on preliminary analysis of the wearable sensor data. We will assess the relationship between wearable sensor parameters (such as heart rate variability, physical activity, and posture) and self-reported pain intensity in participants with chronic visceral pain. We aim to determine whether specific physiological markers—such as body posture— can reliably predict or associate with pain levels. This analysis will provide clinically useful insights into how wearable sensor data can be used to quantify and monitor visceral pain in real-time.

The **secondary endpoints** will focus on exploratory analyses, including:

Pinpointing the functional pathways involved in the development and progression of chronic visceral pain through genetic analysis. This will help us understand why some individuals develop severe pain while others do not, even with similar disease activity.Identifying genetic variants that may regulate visceral pain, particularly in individuals whose pain severity does not align with the activity of their disease. This analysis will explore both known and novel genetic factors that contribute to pain perception.Investigating the presence and concentration of autoantibodies to explore their potential role in chronic visceral pain and immune-mediated mechanisms that may contribute to pain persistence.Identifying distinct clinical phenotypes of visceral pain using clustering techniques to group participants by shared characteristics, such as disease type, pain severity, and wearable sensor data. These clusters will be analysed for potential genetic or immune-related differences.Exploring pain frequency, location (using body maps), and time-series data from self-reported pain ratings to uncover patterns that can help characterize visceral pain flares.

By studying these diverse participant groups and collecting detailed physiological, genetic, and self-reported data, this research aims to provide new insights that could lead to improved diagnostics, treatments, and future studies on chronic visceral pain.

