### Wearable sensors

Participants from Extreme Visceral Pain and Healthy Controls cohorts will use two types of wearable sensors to monitor physiological data:

**Chest *wearable sensor*:** The Discovery *ANNE* Chest System is a flexible, rechargeable sensor worn on the upper chest for up to 16 hours daily over 30 days. It tracks heart rate, respiratory rate, skin temperature, and activity level. Participants will answer two questions daily via a mobile app in a tablet linked to the sensor: “Have you had a visceral pain flare today?” and “Have you changed or cancelled an activity due to visceral pain today?”. To encourage adherence to the wearable sensor usage protocol, instructional videos on how to wear the devices were made publicly available and shared with participants (see Supplementary Information). Additionally, Fig 3 is printed and shared with the participants to provide a visual guide with key steps for sensor setup, syncing, and daily use.

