### Primary endpoint analysis

The primary hypothesis we will test is that specific physiological parameters measured by wearable sensors (such as heart rate, physical activity, or respiration) will associate with self-reported pain intensity and specific body postures, such as sitting or lying down. We hypothesize that:

Higher pain scores will associate with reduced mobility and specific postures (e.g., sitting or lying down).Wearable sensor data will provide objective measures that can predict or associate with self-reported pain intensity.

This hypothesis will be tested using a linear multiple regression model with the following four predictors:

1Heart Rate Variability2Physical Activity (as measured by accelerometery)3Posture (sitting, standing, lying down)4Mean daily respiration rate

We expect that a sample size of n = 100 exclusively for the wearable sub-study provides 80% power to detect a moderate effect size (f² = 0.12 or larger) at p < 0.05, assuming four predictors.

For the primary analysis, we will fit a multiple linear regression model with mean daily visceral pain intensity as the dependent variable and the four pre-specified wearable predictors as independent variables. Model diagnostics will include inspection of residual-versus-fitted plots, Q–Q plots, and tests to assess both normality of residuals and multicollinearity between predictors. If substantial non-linearity or heteroscedasticity is detected, we will explore appropriate transformations of predictors or outcome while retaining the same pre-specified predictor set. All analyses will be conducted using validated statistical packages (either in R or Python), and the final model specification, diagnostics, and code will be documented to support reproducibility.

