Missing data will be addressed using a complete-case analysis approach. No imputation methods will be applied for the wearable sensor data. Analyses will be restricted to participants with valid data for all variables included in the respective models. The extent and pattern of missingness will be reported descriptively. Where appropriate, we will perform sensitivity analyses to assess whether the exclusion of participants with missing data materially affects the results. For transparency, we will report the number of participants and observations included and excluded from each primary and sensitivity model in a CONSORT-style flow diagram and accompanying table. We will also present summary characteristics of participants with and without complete wearable data to allow readers to assess potential selection bias. This approach is justified by the observational nature of the study and the focus on real-world feasibility and data integrity.

This pre-specified analysis aligns with the SPIRIT recommendations for defining and justifying primary hypothesis-testing outcomes in clinical research protocols. All other objectives in this study, including genetic, immunological, and clustering analyses, are exploratory and will be pursued as hypothesis-generating efforts as more data becomes available.

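### Read together, two sections make pain severity and wearable data both clustering inputs and comparison variables, so any p-values on them would be circular

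*Protocol article*

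**What the plan says.** Two sections of the protocol article describe the clustering.

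- **Aims and endpoints (secondary endpoints).** Phenotypes are to be found "using clustering techniques to group participants by shared characteristics, such as disease type, pain severity, and wearable sensor data". The next sentence gives the use of the clusters: "These clusters will be analysed for potential genetic or immune-related differences".
- **Secondary endpoint analyses.** Clustering is applied to phenotype data "to identify subgroups of participants who share similar clinical characteristics". The variables are not listed. The following sentence is: "These subgroups will then be analysed for differences in pain severity, pain location (using body maps), and wearable sensor data". Correlation of the clusters with genetic data comes after that.

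The paragraph on body maps, in the same section, adds hierarchical clustering with "Euclidean distance on scaled variables". It promises that the linkage will be pre-specified, without naming it here, and that the criteria for the number of clusters will be reported.

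On status, Primary endpoint analysis says: "All other objectives in this study, including genetic, immunological, and clustering analyses, are exploratory". On who has sensor data, Wearable sensors says: "Participants from Extreme Visceral Pain and Healthy Controls cohorts will use two types of wearable sensors".

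**The concern.** A cluster algorithm assigns people to groups so that the groups differ on the variables fed into it. Comparing the groups afterwards on those same variables tests something the algorithm has already arranged, and an ordinary test has no valid null distribution. Pain severity and wearable data appear by name in both places: as clustering characteristics in one section and as comparison variables in the other. Nothing in the article removes them from the inputs, holds data back, or limits the comparison to description.

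The risk is that small p-values on pain or sensor measures are taken as evidence that the phenotypes are real. The same clusters are then carried into the genetic and immune work, so a weak foundation would spread.

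**Working it through.** **Step 1: the two sections side by side.**

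| | Aims and endpoints | Secondary endpoint analyses |
|---|---|---|
| Clusters formed from | disease type, pain severity, wearable data (as examples) | phenotype data, not itemised |
| Clusters compared on | genetic and immune variables | pain severity, pain location, wearable data; then correlation with genetic data |

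Neither column is circular alone. Joining the inputs on the left to the comparisons on the right makes pain severity and wearable data both input and outcome. Pain location joins them only if body maps also enter the clustering.

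**Step 2: inputs to the check.** The plan gives no figure for this analysis, so there is none to reproduce.

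- From the article: Euclidean distance on scaled variables; n = 100, from "a sample size of n = 100 exclusively for the wearable sub-study"; n = 350, the total in Participant recruitment.
- Assumed, because the article does not fix them: 5 or 10 clustering variables; k = 2, 3 or 4 clusters; Ward, complete, average or single linkage, or k-means; alpha 0.05, as in the primary analysis.

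This gives 2 × 2 × 3 × 5 = 60 settings, with 300 simulated datasets each.

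**Step 3: method.** All variables are independent standard normal, so no true clusters exist. The inputs are scaled and clustered. Each variable is then compared across clusters with one-way ANOVA:

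F = [SSB/(k − 1)] / [SSW/(n − k)], where SSB and SSW are the between- and within-cluster sums of squares.

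The reference F distribution requires labels chosen without looking at the variable. For an input, SSB + SSW is fixed and the algorithm picks labels that make SSW small, which pushes F up. The same number of independent variables, kept out of the clustering, is tested for comparison.

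**Step 4: results for input variables.** Average percentage of inputs with p<0.05, for k = 2 / 3 / 4 (nominal 5%):

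| Method | n = 100, 5 inputs | n = 100, 10 inputs | n = 350, 5 inputs | n = 350, 10 inputs |
|---|---|---|---|---|
| Ward | 71 / 89 / 97 | 56 / 77 / 88 | 82 / 95 / 99 | 70 / 89 / 96 |
| Complete | 63 / 85 / 95 | 47 / 65 / 80 | 76 / 93 / 99 | 60 / 81 / 91 |
| Average | 40 / 58 / 75 | 25 / 37 / 47 | 42 / 66 / 80 | 29 / 44 / 55 |
| Single | 31 / 42 / 47 | 21 / 27 / 31 | 36 / 50 / 57 | 25 / 33 / 40 |
| k-means | 76 / 94 / 98 | 62 / 82 / 90 | 85 / 98 / 99.9 | 78 / 93 / 98 |

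The rate for a single input therefore runs from 21% to 99.9%. At least one input reached p<0.05 in 98.0% to 100% of datasets in every setting, and in 100% with Ward, complete linkage and k-means.

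**Step 5: results for variables kept out.** The rate was 3.8% to 6.1% over all 60 settings. Both extremes occurred with five variables, where the simulation error is √(0.05 × 0.95 / (300 × 5)) = 0.56 percentage points. They lie about 2 standard errors from 5%, which is unremarkable for the extremes of 60 settings.

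**Step 6: who can be clustered.** Wearable sensor baseline, Wearable sensors and the Fig 1 legend give sensors to the Extreme Visceral Pain and Healthy Controls cohorts only. Primary endpoint analysis adds that not all of the Extreme cohort will wear them. A Euclidean distance cannot use a value that was never collected, so any clustering with wearable inputs cannot place these participants.

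**The case against.** The best defence is that the analysis section can be read as sound by itself: cluster on clinical characteristics, then compare on pain and sensor measures. The endpoint section is also sound by itself, and its wording introduces the inputs as examples, not as a closed list. An exact input list for an exploratory analysis may also be left to a fuller document. This stands as far as it goes, and it is why the point is conditional on following both sections. It does not dispose of the point: the article does state inputs and comparisons, the two sections differ on the inputs, and the named variables overlap.

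Second, no test is named. Profiling clusters on their own inputs is normal and harmless when it is only descriptive. That is correct, and the inflation applies only if p-values are produced. But the sentence does not say the comparison is descriptive, whereas the autoantibody and body-map analyses in the same section are called descriptive statistics.

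Third, the simulated rates depend on settings that the plan leaves open. The distance metric sits in the body-map paragraph, disease type is categorical, and real variables are correlated. The rates are therefore illustrations and not properties of this plan.

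Two stronger readings are tempting and are not supported:

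- A reader might infer that significant differences in pain severity and wearable data are guaranteed. Near-certainty holds for at least one input, not for a particular named variable.
- A reader might infer that the Lack of Visceral Pain cohort will be dropped from the phenotyping. The complete-case rule stands in the primary-analysis text, and no section requires wearable data as an input for every participant or a single clustering of all cohorts. Table 1 also covers both patient cohorts in its wearable eligibility criteria, although the procedural sections give sensors to only one of them.

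**Conclusion.** The concern holds in conditional form. The two sections need reconciling, and if both are followed with p-values, the comparisons of clusters on pain severity and wearable data are circular. Under the assumed settings, pure noise gives at least one input at p<0.05 in 98% to 100% of datasets and a single input in about 21% to 99.9%, against about 5% for variables left out of the clustering.

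The genetic and immune comparisons are not affected. Nor is pain location, unless body maps are used as inputs. The exploratory status lowers the consequence but does not make a circular comparison informative. The loss of participants without sensors is secondary, and arises only if wearable data stay among the inputs.

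**What to change.** - Make Aims and endpoints and Secondary endpoint analyses name the same clustering inputs.
- Restrict inferential comparisons to variables not used to form the clusters. For example, cluster on clinical variables, then compare on pain severity, wearable, genetic and autoantibody data.
- Report any variable that remains an input by cluster, descriptively and without p-values. If body maps are inputs, treat pain location in the same way.
- Preferably keep wearable data as an outcome, so that participants without sensors, including the Lack of Visceral Pain cohort, can still be assigned to clusters.

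The cost is a few sentences of analysis-plan wording. Study status reports that no data have been analysed, so the change can be made before any results are seen. The one real downside is that the clusters no longer draw on the variables held out.

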### Study status

Recruitment for the study began on 1st November 2023 and is currently ongoing. Completion of participant recruitment is anticipated by 30th June 2026. Data collection is being conducted in parallel with recruitment and is expected to conclude by 31st December 2026. No data analysis has been performed, and no results have been generated at this stage. Preliminary results are expected to be available by 30th June 2027, following the completion of data collection and initial data processing. The current manuscript describes the study protocol only and does not include or imply any outcome data.

### Ethics and dissemination

This study involves human participants and was approved by the Health Research Authority, Health and Care Research Wales (23/PR/058), and the London-Surrey Research Ethics Committee. The Cambridge University Hospitals NHS Foundation Trust and the University of Cambridge are joint sponsors of the study (Sponsor No. A096518, IRAS ID 322886).

All participants provide written informed consent prior to enrolment in the study. Signed consent forms are securely stored in accordance with NHS and sponsor policies. No verbal consent procedures are used, and no consent waivers were granted by the approving ethics committees. Template consent forms for each participant cohort are provided in the Supplementary Information.

The study will follow the principles of the International Conference on Harmonization’s Guideline for Good Clinical Practice (ICH GCP). The Chief Investigator is responsible for the study’s overall conduct and compliance and may delegate certain responsibilities to appropriately trained staff.

Participation in the study is voluntary, and participants will be provided with Information Sheets (see Supporting Information). The Investigator must ensure all staff are informed about the study protocol and their specific duties. Local Investigator Site Files (ISFs) will contain all required documentation.

Researchers with data access must be trained in data protection regulations, including the UK General Data Protection Regulation and Data Protection Act 2018. All data will be securely stored, and clinical information will only be released with the participant’s written permission. Personal data will be held in a secure safe haven, accessible only via multi-factor authentication, and anonymized linked data will require usernames and passwords for access.

Ownership of the study data resides with the protocol lead and co-lead authors. Results will be disseminated through peer-reviewed publications, lay summaries, and collaborations with the Patient Charity Advisor Board. Published results will not contain personal data or any information that could lead to re-identification.

### Patient and public involvement

Patients were involved in the design, conduct, reporting, and dissemination plans of this research through the ADVANTAGE Patient and Charity Advisory Board. A summary of the Board’s contributions to the study and protocol can be found in the Supplementary Information.
